##### Provider-level descriptives

The following basic demographic and clinical experience data will be collected from providers enrolled in the study at baseline: age, gender, race, ethnicity, educational attainment, employment status, position title, number of years in practice, level of experience treating patients with HIV and substance use, knowledge of HIV and substance use treatment, and prior training experience. Providers will also complete measures indicating their willingness to participate in the study and their perceptions of stigma related to dual care. The *Coercion Assessment Scale* (CAS) [36, 37] is an 8-item measure of voluntariness to participate in research. The *Provider Perception Inventory* [38] is a 39-item scale that measures health service providers’ stigma in regards to HIV, substance use, and MSM behavior, which will be used to measure provider-related stigma.

##### Provider acceptability and usability of the CCI

We will measure providers’ perceived acceptability of and satisfaction with the CCI, as well as their perceptions of the intervention. Provider acceptability data will be gathered primarily through qualitative exit interviews at the 6- month follow-up. Providers will also be asked to complete a program satisfaction survey which will assess level of satisfaction for each component of the CCI. Perceptions of the intervention will be measured via the Perceived Attributes Scale, a 27-item, customizable scale that measures five aspects of an intervention or innovation (i.e., Relative Advantage, Compatibility, Complexity, Trialability, Observability) that have been shown to influence adoption.

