Key stakeholders (n = 8 in Phase 1: stakeholder interviews) and frontline HIV and SUD treatment providers (n = 8 in Phase 2: functionality testing; and n = 60 in Phase 3: Pilot Trial) will be recruited from the HIV and SUD clinics. Upper management in each organization will inform providers that participation in the study is available and they may volunteer to participate; providers will be explicitly informed that participation is voluntary and will not affect their employment. Once a potentially eligible provider has been identified, the RA will contact the provider, introduce the study, and assess eligibility. For inclusion, key stakeholders must: (a) be at least 18 years of age, (b) have a major administrative or leadership role (i.e., President/CEO, Clinic Director, Executive Leadership) in an HIV or SUD treatment center, (c) have been employed in their current leadership position for at least 6 months, and (d) able and willing to provide informed consent. Treatment providers must: (a) be at least 18 years of age, (b) provide either HIV care or SUD treatment [e.g., physicians, residents, psychologists, mid-level providers], (c) have been employed at a participating recruitment site for at least 6 months, (d) have no plans for a leave of absence over the next 2 years and (e) willing and able to provide informed consent. We will recruit an even number of stakeholders and providers from HIV and SUD treatment centers. We recognize that staff turnover may occur throughout the study and especially during Phase 3 (6-month intervention phase). Providers who leave employment during the trial period will be asked to return the tablet device to the study and will be removed from participating in the CCI for the remainder of the study. Participants in Phase 1 (stakeholder interviews) will receive $75, and participants in Phase 2 (functionality testing) will be paid $50. In Phase 3 (pilot trial), participants will be paid $50 for completion of the baseline interview and $40, $45, and $50, respectively, for completion of the 1-, 3- and 6-month follow-ups. Participants completing exit interviews will receive an additional $50.

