##### Training procedures

Although the primary aim of the proposed study is intervention development, we are mindful of the need to have an evidence-based replicable training protocol to facilitate widespread implementation. We use the Service to Science Laboratory (SSL) staff training model, which was specifically developed by the SAMHSA-funded Addiction Technology Transfer Centers (ATTCs) to increase support for intervention adoption at both the individual-level and organizational-level. The SSL model contains three key elements: upfront didactic training, ongoing performance feedback, and ongoing coaching from an external leadership coach who works with Internal Change Champions within each organization [34].

The upfront didactic training will be led by a member of the New England ATTC staff and will consist of three training sessions (see Table 2 for an overview of topics). Participants will complete a 20-item baseline knowledge assessment prior to Training Session #1. All training sessions will be audio-recorded and participants who are unable to attend will be required to listen to the audio recording and attend a brief make-up training session. Upon completion of Training Session #3, each treatment provider will be required to complete a 20-item post-training knowledge assessment and to demonstrate adequate knowledge, defined as accurate answers to 16 (80%) of the items. Each provider will also complete a role play with the ATTC trainer using a standardized patient case. During the role play, the provider will be required to demonstrate competence in the following six areas: (a) identifying resources to detect patients in need of dual care, (b) using the referral system (including ability to both make a referral and accept a referral request), (c) tracking of patients’ access and utilization of services, (d) reading real-time patient care notifications, (e) identifying a patient’s care team, and (f) reviewing up-to-date lists of resources and evidence-based recommendations for treatment options. Providers who do not demonstrate competence will receive immediate corrective feedback and up to two additional role plays will be conducted until competence is shown. Only those providers who exhibit competence in all six areas will proceed to the next phase of training.

**Table 2 Tab2:** Expected features and benefits of the care coordination intervention (CCI) based on preliminary qualitative work

Training procedures	

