After completion of the 3-session didactic training series, we will enable the mobile application, assign each provider a tablet device, and initiate the 6-month open trial. At this point, the SSL training model will shift from a focus on didactics to ongoing interpersonal support. The SSL relies heavily on supportive interpersonal personal strategies through the use of an external leadership coach and Internal Change Champions, who continually encourage collaborative problem solving throughout the organization. The eight key stakeholders will be responsible for either serving as Internal Change Champions or selecting alternates. The external leadership coach will have monthly coaching calls with the Internal Change Champions focused on tracking implementation progress and engaging in problem solving to address barriers to sustained use of the mobile application. In turn, the Internal Change Champions will be responsible for providing ongoing supervision and support to frontline treatment providers. Consistent with the recommendations of Montague et al. [18], who noted the need for cross-training among HIV and substance use providers, the SSL will include cross-training via explicit didactic instruction and ongoing coaching in an effort to increase understanding of each provider’s role and disease specific processes.

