##### Measures

The framework identified in Fig. 1 has informed the battery of measures. Assessments will focus on organizational-, provider-, and patient-level domains (see Table 3). Primary outcomes will be feasibility and acceptability of the CCI and assessment procedures to be used in a larger trial [35]. Organizational outcomes will include pre- and post-intervention assessments of each clinic to gather data on organizational structure and procedures for care coordination. Provider outcomes will include feedback on the intervention component in Phase 1 and 2 of the trial; satisfaction of care coordination, frequency and quality of interagency communications, and interagency professional relationships; and potential moderators (e.g., stigma, perceived coercion). Patient outcomes will include demographics, viral load, and retention in dual care. Quantitative measures will be collected via web-based surveys from clinic leadership (n = 8) and providers (n = 60) at baseline and 1-, 3-, and 6-months post implementation of the CCI (Phase 3).

**Table 3 Tab3:** Outcome variables and assessment points

Quantitative measures	BL	Post-T	1-, 3- mos	6 mos	Analysis
Provider-level outcomes					
Provider descriptive information					
Provider demographics	X				Descriptive
Training in HIV and SU issues	X		X	X	Descriptive
HIV/SU treatment experience	X		X	X	Descriptive
Knowledge related to SU/HIV	X	X		X	Descriptive
Coercion assessment scale	X		X	X	Exploratory: Moderator
Provider perception inventory	X		X	X	Exploratory: Moderator
Provider acceptability and usability of the CCI and training protocol					
Satisfaction with training		X			Acceptability
CCI program satisfaction				X	Acceptability
Perceived attributes scale	X		X	X	Exploratory: Mediator
Interagency collaboration and communication					
Levels of collaboration scale*	X		X	X	Quant: Hyp 2
Frequency/quantity of communication*	MDE		MDE	MDE	Quant: Hyp 2
Wilder collaboration factors inventory	X			X	Exploratory: Moderator
Relational coordination					
Relational coordination scale*	X		X	X	Quant: Hyp 3
Organizational-level outcomes					
Organizational descriptives	X			X	Descriptive
Organization readiness	X		X	X	Exploratory: Mediator
Implementation climate scale	X		X	X	Exploratory: Mediator
Patient-level outcomes					
Descriptive information					
Demographics	MDE				Descriptive
Viral load	MDE			MDE	Descriptive
Dual care treatment retention	C/MDE			C/MDE	Quant: Hyp1

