##### Preliminary assessment of implementation context

Although this study is an intervention development study, the mixed-methods design will allow us to gather preliminary data in regards to implementation context and information transfer that inform future multisite trials. We will conduct individual qualitative interviews with 4–5 key stakeholders at 6 months following implementation of the CCI. These interviews will gather data regarding perceptions of providers and leadership concerning barriers and facilitators to CCI adoption, tools needed to deliver the intervention consistently, resources needed to maintain the CCI long-term, and adaptations needed to integrate the CCI into regular practice. Qualitative data from exit interviews will be triangulated to examine themes related to barriers and facilitators of CCI adoption, stakeholder and organizational satisfaction with the CCI, and acceptability of the CCI. Additionally, we will measure the following costs associated with CCI implementation: training hours (study staff and provider time) and equipment and other resources costs.

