#### Hypotheses testing

Given the developmental nature of this study, our primary objective is to establish feasibility and acceptability of the CCI and assessment procedures. The following deliverables will result from this study: evidence-based training model adapted to HIV and substance use providers, mobile application tool for providers targeting care coordination, interagency communication protocol, and a training strategy for the CCI. This study will yield necessary data regarding the acceptability and feasibility of the approach to be implemented in a future larger scale multisite trial [35]. We are well aware of the dangers of relying exclusively on small-scale pilot studies to gauge the promise of a novel intervention [43]. Thus, we primarily will be hoping to find a pattern of results that is supportive of the CCI rather than rigorously testing hypotheses to determine a stable effect size. Hypotheses include: (1) Compared to baseline, providers will demonstrate increased dual care treatment retention as measured by data in the EHR; (2) Compared to baseline, HIV providers will report increased frequency and quantity of communication with substance use providers, and substance use providers will report increased frequency and quantity of communication with HIV providers; and (3) Providers will report improvements in relational coordination as measured by increased scores on the Relational Coordination scale between baseline and follow-up assessment. Group means on continuous variables typically begin to stabilize around 15 participants per group. For dichotomous variables, somewhat larger sample size is needed to provide reasonably stable odds ratios for effect size estimates. Therefore, the proposed sample size of 30 participants per group, even after attrition, will allow us to evaluate the potential of the CCI intervention to improve care coordination while remaining within the budgetary parameters for a preliminary trial.

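### Acceptability, one of the two primary outcomes, may be overstated: its main data come at 6 months with no stated route to providers who failed training or left, and leaders who finalised the CCI also feed into it

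*Protocol article*

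**What the plan says.** The Measures section of the protocol article states: "Primary outcomes will be feasibility and acceptability of the CCI and assessment procedures to be used in a larger trial". The Hypotheses testing section repeats this as the primary objective and ties it to a future multisite trial. (Table 3 puts its primary-outcome asterisk on other variables; this point rests on the text.)

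For the source of the acceptability data, the section on provider acceptability and usability says: "Provider acceptability data will be gathered primarily through qualitative exit interviews at the 6- month follow-up". It adds a programme satisfaction survey, which Table 3 marks at 6 months only.

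Two filters come before that assessment:
- Training procedures: "Only those providers who exhibit competence in all six areas will proceed to the next phase of training". The preceding sentence softens this: "Providers who do not demonstrate competence will receive immediate corrective feedback and up to two additional role plays will be conducted until competence is shown".
- Participants and setting: a provider who leaves employment returns the tablet and "will be removed from participating in the CCI for the remainder of the study".

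On leaders, the section on implementation context says: "We will conduct individual qualitative interviews with 4–5 key stakeholders at 6 months following implementation of the CCI". It then lists acceptability of the CCI among the themes drawn from exit-interview data. Under the Phase 2 refinement heading, the eight Phase 1 stakeholders meet the investigators to review changes and finalise the CCI. Training procedures adds: "The eight key stakeholders will be responsible for either serving as Internal Change Champions or selecting alternates".

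**The concern.** A provider who found the CCI hard to learn, or who left during the trial, is a plausible source of unfavourable opinion. The two main acceptability sources, the exit interview and the CCI satisfaction survey, are both timed at 6 months, and nothing stated brings them forward for someone who goes earlier. Followed as written, the plan gives a reading from completers.

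The leaders raise a second, separate problem. They help finalise the product and either champion it or choose who does, so they are not independent judges of it. If their interviews are merged with those of frontline providers, a favourable theme cannot be traced to the people who had to use the app.

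The study has no control condition and modest aims for hypothesis testing, so acceptability carries much of the weight in deciding whether a larger trial is worthwhile. An inflated reading would bear directly on that decision.

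**Working it through.** **Inputs**
- Enrolled in Phase 3: 30 + 30 = 60 providers (Abstract; Hypotheses testing).
- Follow-up: the Missing data section cites rates above 90% in similar studies. At 90%, 60 × 0.90 = 54 are rated and 6 are not.
- A 20% combined loss (training check plus turnover), leaving 48 rated, is my assumption. The article gives no rate for either filter.
- Satisfaction among responders of about 85% is assumed. The article gives no expected value.
- Satisfaction among those not rated, *q*, is unknown and is varied.

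**The plan's own figure.** There is none for acceptability to reproduce. The 30 per group rests on a rule of thumb about when means stabilise, without a power or precision formula.

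**Formula.** With *m* providers rated and a share *p* of them satisfied:

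full-cohort satisfaction = [*m* × *p* + (60 − *m*) × *q*] / 60

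overstatement = *p* − full-cohort satisfaction

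**Results**

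| Rated | Among responders | *q* for those not rated | Over all 60 | Overstatement |
|---|---|---|---|---|
| 54 | 46/54 = 85.2% | 0 | 46/60 = 76.7% | 8.5 points |
| 54 | 46/54 = 85.2% | 50% (3 of 6) | 49/60 = 81.7% | 3.5 points |
| 54 | 46/54 = 85.2% | 85.2% | 85.2% | 0 |
| 48 | 41/48 = 85.4% | 0 | 41/60 = 68.3% | 17.1 points |
| 48 | 41/48 = 85.4% | 50% (6 of 12) | 47/60 = 78.3% | 7.1 points |
| 48 | 41/48 = 85.4% | 85.4% | 85.4% | 0 |

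Starting from 80% among responders, the worst case (*q* = 0) is 54 × 0.80 / 60 = 72% at 10% loss and 48 × 0.80 / 60 = 64% at 20% loss, so the scale is similar.

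Rows with *q* = 0 are bounds, not estimates, so no confidence interval is attached. The figures apply to the satisfaction survey. The exit interviews are qualitative and yield no proportion, but the same people are absent from them unless steps are taken to reach them.

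**Which measures could reach those who go early?** Going through Table 3:
- Satisfaction with training is labelled an acceptability measure and is taken post-training. It precedes live use, since the app is enabled only after the didactic series.
- The Perceived Attributes Scale is given at baseline and at 1, 3 and 6 months, so some later leavers contribute. It is labelled an exploratory mediator.
- CCI programme satisfaction is at 6 months only.

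So the measures labelled as acceptability include one before live use and one at 6 months, with none in between.

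**The case against.** The strongest reply is that the gap is small and partly covered. Follow-up above 90% would leave at most about 6 of 60 unrated. Corrective feedback and two further role plays may mean that few fail the check, and nothing shows that those who fail are dissatisfied. Leavers are taken off the CCI, but no sentence bars them from a survey or an interview, and reasons for dropout are to be collected where possible. Provider acceptability is expressly sought from providers, and paid exit interviews appear among the Phase 3 participant payments. How many are interviewed and how they are chosen is detail that an article may leave to the full protocol.

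Most of this stands, and it rules out several stronger readings that a reader might draw:
- *That feasibility too is judged only in completers.* Usage is logged throughout, reach is measured over all eligible providers with reasons for declining, and dropout rates and reasons are examined. These data cover decliners and leavers.
- *That the least satisfied are never asked.* Training satisfaction is collected before live use, and the Perceived Attributes Scale continues during follow-up. What is lacking is a stated provision to obtain the main acceptability data.
- *That no result could count against the CCI,* because "we primarily will be hoping to find a pattern of results that is supportive of the CCI". That sentence goes on to contrast this aim with rigorous hypothesis testing and leads into the hypotheses on retention, communication and relational coordination. It is not evidently the yardstick for acceptability, and progression thresholds may sit in the full protocol.
- *That leaders are the main acceptability informants.* Their interviews sit under implementation context and supplement the provider data.

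What the reply does not remove is the timing. Training satisfaction cannot speak to the app in use, and multiple imputation of outcome data cannot stand in for an interview that did not take place.

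**Conclusion.** The point holds for acceptability, as a risk of overstatement rather than a demonstrated bias. The satisfaction survey is fixed at 6 months, the exit interviews are placed there too, and no provision is stated for providers who fail training or leave. Leaders with a hand in building and promoting the CCI also contribute to the acceptability themes.

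With responder satisfaction assumed at about 85%, the overstatement is at most about 8.5 points at 10% loss and about 17 points at an assumed 20% loss. It is roughly 3.5 and 7 points if half of those lost would have been satisfied, and nil if they resemble the rest. The upward direction depends on those lost being less satisfied, which is plausible but not shown in the article. The size depends on losses the article does not state. The change is worth making because it is cheap and touches a primary outcome.

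**What to change.** 1. Give the existing CCI satisfaction survey when a provider leaves or does not pass the competence check, as well as at 6 months. Those who never used the app should answer only the items on training and the communication protocol.
2. Offer the already paid exit interview to frontline providers, expressly including low users (identifiable from the dashboard) and leavers.
3. Report acceptability from leaders separately from that of providers.
4. Report satisfaction among responders as the main figure and, beside it, the all-enrolled figure over 60 as a sensitivity lower bound. Counting every leaver as a non-acceptor should not be the primary definition, because ordinary staff turnover is not rejection of the CCI and the result would be pushed downward by construction.

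The cost is some wording and one short extra survey for those who go early; payment for exit interviews is already foreseen. The downside is that reported acceptability may be lower. Neither the intervention nor the training check needs to change.

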##### Interagency collaboration and communication

CCI usage will be measured via the mobile application dashboard throughout the study. The Levels of Collaboration Scale [39] will be adapted for the purposes of this study and will measure progress over the five levels of collaboration and their characteristics (networking, cooperation, coordination, coalition, collaboration). The Wilder Collaboration Factors Inventory [40] is a 40-item measure that assesses strengths and weaknesses within organizations shown to be important for successful collaborations. Factors include: collaboration history, organizational climate, mutual respect, definition of roles, adaptability, and shared goal setting.

##### Relational coordination

A Relational Coordination Scale will be developed by the investigative team as there are no available measures assessing these constructs. This measure will include items assessing the following constructs: definition and awareness of provider roles in the co-management of HIV and substance use; quality of relationships between clinic providers (e.g., mutual respect, collaboration); exchange of information (e.g., transfer of information, ideas, and opinions); and setting and sharing of common goals.

##### Organizational-level

We will evaluate organizational-level descriptive characteristics as well as putative organizational mediators of CCI usage. Descriptive organizational data from participating clinics will be collected during both pre- and post-implementation site visits and include (a) number of patients at each clinic diagnosed with comorbid HIV/SUD enrolled in care; (b) number of patients receiving care at the SU clinic who are referred to testing and number tested for HIV, number of patients referred to HIV care or PrEP; (c) number of patients receiving care at the HIV clinic who are assessed for a substance use problem and number referred for substance use treatment; (d) number of patients receiving co-management care of HIV and substance use. At the 6-month post-implementation assessment, will measure also measure CCI Reach by tracking the percentage of eligible providers who participated and reasons providers chose not to participate. We will measure Organizational Readiness to Implement Change and Implementation Climate as putative mediators of CCI adoption at baseline, 1, 3, and 6 months. The Organizational Readiness for Implementing Change (ORIC) [41] questionnaire is a 12-item measure on a five-point scale, 1 (“disagree”) to 5 (“agree”). This scale will be administered to providers and key stakeholders to determine the extent to which there is a shared perception of organizational readiness for the CCI. The Implementation Climate Scale [42] will measure the degree to which there is a strategic organizational climate supportive of intervention implementation. This is a 38-item questionnaire that is scored on a five-point scale, 0 (“not at all”) to 4 (“very great extent”).

